#### Plans to Promote Participant Retention and Complete Follow-Up

Participant retention will be implemented following the methods adopted in our previous project, which included communication via the project’s Facebook account and regular information dissemination to the participating communities through the study community reference group. Direct contact with study participants will also be maintained through email contacts.

#### Data Management

Data will be collected through the REDCap implementation on an iPad. Data entries will have range checks and data validation. All data entries will be performed via a password-protected iPad, which will be stored in locked cabinets situated within locked offices, accessible only to the research personnel.

### Statistical Methods

#### Statistical Analyses for Primary and Secondary Outcomes

Analyses will be on an intention-to-treat and per-protocol basis. Objectives 1 to 3 will be tested using a test of proportions and logistic regression and negative binomial regression for overdispersed count data, accounting for clustering within individuals and communities. Subgroup objective 4 will be tested using paired tests for pre- and postintervention changes in COHRQol and dental anxiety as well as unpaired tests for between-group differences at baseline and follow-up; multivariable analyses will use generalized estimating equation linear regression to control for teeth and community clustering. Objective 5, economic analyses, will be tested as outlined in the subsequent section. All analyses will be undertaken by analysts who are blinded to group allocation status, and take into account clustering within communities and baseline factors and any baseline intergroup differences. Multiple imputations of missing data will be undertaken to evaluate its impact on the primary and secondary outcomes.

Objective 6 will be evaluated through qualitative analyses of the focus group interviews, with all interviews digitally recorded and independently transcribed. Transcripts will be read, and coding will be undertaken by analysts who are blinded to group allocation status. A thematic analytical approach will be adopted to develop themes and explore the contextual differences among the perceptions, experiences, and beliefs without a strict requirement for a theoretical focus [23,24]. Transcripts will be read multiple times to establish familiarity with the dataset. Two independent reviewers, one of whom will be an Indigenous researcher, will develop a coding scheme of the transcripts and also develop emerging themes. Where disagreement in coding is identified, the differences will be resolved through discussion and consensus. Our approach will broadly follow a reflexive thematic analysis (based on the study by Braun and Clarke [24]), drawing on subjective interpretations of both an Indigenous and a non-Indigenous researcher. The emergent themes will be explored and further refined. Data management will be facilitated using NVivo (version 12; Lumivero). Objective 7 will be evaluated by calculating sensitivity, specificity, predictive values, and receiver operating characteristics, validated against on-site clinical assessment.

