### Objectives

The principal aim of the proposed study is to evaluate the feasibility of using the skills of an appropriately trained Aboriginal health practitioner or worker to undertake the application of AgF to carious primary molars of young Aboriginal children in remote communities and evaluate the effectiveness and acceptability of AgF, using a 2-arm cluster RCT. It will also validate the use of teledentistry to diagnose and prescribe treatment remotely. The outcomes will be compared with those of the alternative care model using the recently tested ART and HT approach, delivered by an oral health professional team, for clinical outcomes, cost-effectiveness, cost utility, child oral health–related quality of life (COHRQoL), and child dental anxiety. The objectives of the project are as follows:

The first objective is to measure the number of teeth and tooth surfaces with arrested carious lesions and restored at baseline and follow-up. The hypothesis is that *the number of arrested carious lesions will be greater in the intervention group at follow-up.*

The second objective is to measure the number of teeth and tooth surfaces with dental decay and new decay and the number of teeth with dental infections among study participants at baseline and follow-up. The hypothesis is that *the number of children with newly active decay in their teeth and tooth surfaces and new dental infections in the intervention group will not be greater than the specified difference (risk difference) deemed to be a noninferior outcome.*

The third objective is to measure the extent of discoloration in teeth treated with AgF, with or without KI. The hypothesis is that *the extent of discoloration will be less in the intervention group treated with AgF and KI.*

The fourth objective is to measure the change in COHRQoL and dental anxiety using validated measures. The hypothesis is that *the extent and number of children with improved COHRQoL and dental anxiety in the intervention group will not be any less than the specified difference (risk difference) deemed to be noninferior.*

The fifth objective is to evaluate the cost-effectiveness and cost utility of the interventions. The hypothesis is that *the intervention will be less costly with a noninferior outcome.*

The sixth objective is to evaluate the acceptability of the interventions between the 2 groups of participants through focus group interviews using the “yarning” approach [12].

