## Methods

### Trial Design

This study will use a robust, pragmatic, 2-arm parallel group cluster randomized, active-controlled, noninferiority trial design. This study will be reported according to the CONSORT (Consolidated Standards of Reporting Trials) guidelines on reporting of noninferiority trials [13]. Study communities will be randomized into test or control groups by a central study coordinator through a computer-generated block randomization procedure, stratified by expected decay experience and exposure to community water fluoridation levels based on findings from our earlier work in the Kimberley region [6]. Both arms of the study will be provided with dental care; the control arm will be treated using the ART and HT approach, and the test arm will be treated using AgF. The test group will be further randomized into 2 groups via computer-generated allocation in concealed envelopes at study sites to receive 1 of the 2 AgF formulations. One formulation will have 38% AgF and KI as a staining reducing agent (Riva Star Aqua; SDI Limited); the other formulation will have 40% AgF with stannous fluoride as a reducing agent (Creighton Dental AgF; Whiteley Corporation). The Riva Star Aqua group will be further randomized to receive KI or no KI to evaluate KI’s effect on reducing the staining associated with AgF and evaluate its impact on caries arrestment. Moreover, we will evaluate the COHRQoL [14] and child dental anxiety and undertake an economic evaluation of the interventions. Focus group interviews, using the yarning approach, will be conducted to better understand the impact of the dental treatments [12]. We will also test the effectiveness of teledentistry in caries diagnosis and treatment prescription. Participants will have digital images taken of their dentition with a smartphone using standardized procedures [15]. The images will be stored and sent securely to a calibrated assessor at a remote site. The assessor, blinded to group allocation, will evaluate the images and diagnose and prescribe treatment.

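### As written, the named analyses do not deliver the risk-difference noninferiority conclusions set for objectives 2 and 4, most clearly for objective 4

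*Protocol article*

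**What the plan says.** Trial Design in the protocol article describes a "2-arm parallel group cluster randomized, active-controlled, noninferiority trial design". Under Objectives, the objective 2 hypothesis is that the number of children with new active decay or new infection "will not be greater than the specified difference (risk difference) deemed to be a noninferior outcome". The objective 4 hypothesis is that the extent and number of children with improved oral health-related quality of life (COHRQoL) and dental anxiety "will not be any less than the specified difference (risk difference) deemed to be noninferior". The difference is called specified, but no number is given anywhere in the article.

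The section Statistical Analyses for Primary and Secondary Outcomes then names the methods. "Objectives 1 to 3 will be tested using a test of proportions and logistic regression and negative binomial regression", with allowance for clustering within individuals and communities. Objective 4 is tested by "paired tests for pre- and postintervention changes in COHRQol and dental anxiety as well as unpaired tests for between-group differences at baseline and follow-up", and its multivariable analysis is a GEE linear regression. All analyses are to "take into account clustering within communities and baseline factors and any baseline intergroup differences". Both intention-to-treat and per-protocol analyses are planned. Communities are randomised "stratified by expected decay experience and exposure to community water fluoridation levels"; the analysis section names neither factor as a covariate.

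**The concern.** A noninferiority claim needs a between-arm estimate on the scale and unit of the hypothesis, with a confidence bound compared with a margin. The analysis section names specific methods for objectives 2 and 4, and none is connected to a margin or a bound. For objective 4, none is said to estimate the between-arm difference in the proportion of children improved.

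A noninferiority objective analysed only by tests of difference leaves the reader with significant or not significant, and a non-significant result is not evidence of noninferiority. It is also easier to obtain when the trial is imprecise. In addition, adjusting for whatever differences appear at baseline lets the observed data help choose the covariates, so the adjusted result is not fully fixed in advance.

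**Working it through.** **Hypothesis and analysis side by side**

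| | Objective 2 | Objective 4 |
|---|---|---|
| Hypothesis | Noninferiority, risk difference, children with new decay or infection | Noninferiority, risk difference, extent and number of children improved |
| Methods named | Test of proportions, logistic, negative binomial | Paired pre-post tests, unpaired tests at baseline and follow-up, linear GEE |
| What they give as described | Difference in proportions (for lesions and surfaces, per the Abstract), odds ratio, rate ratio | Within-arm change, baseline contrast, between-arm contrast in scores |
| Gap | Unit is not the child; no bound or margin | No analysis of number improved; no bound or margin |

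For objective 4, a paired test within an arm says nothing about the other arm. A baseline test between randomised arms only asks whether chance produced a difference. The unpaired follow-up test and the GEE do compare arms, but on mean scores.

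**Why the scale matters.** An odds ratio does not translate into one risk difference. With control risk p, the comparison risk is q = 1.5p/(1 − p + 1.5p) at an odds ratio of 1.5, and q − p is:
- p = 10%: 0.043
- p = 30%: 0.091
- p = 50%: 0.100

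These control risks are assumptions. A margin on the risk-difference scale therefore cannot be checked from an odds ratio alone.

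**The plan's own sample size.** Inputs from Sample Size: 61% v 81%, α 0.05, 80% power, 15 communities per arm, ICC 0.09, 25% loss per year.
- A two-sided, continuity-corrected comparison of two proportions gives n0 = 90 per arm.
- With 15 communities fixed, n = n0(1 − ICC)/(1 − n0 × ICC/15) = 90 × 0.91/(1 − 0.54) = 81.9/0.46 = 178.0. That is 12 per community, or 180 per arm.
- Loss: 180/0.75² = 320; 320/15 = 21.3, rounded up to 22.

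The published 180, 320 and 22 are reproduced. Two-sided without the continuity correction gives 140 (150 after rounding to whole children per community); the one-sided versions give 105 or 120 after rounding. The calculation that matches is a test of a 20-point difference with no margin, so the sample size section does not supply the missing number either.

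**Precision for a child-level risk difference.** Assume one binary outcome per child and the planning ICC of 0.09.
- Design effect = 1 + (12 − 1) × 0.09 = 1.99; effective size = 180/1.99 = 90.5 per arm.
- SE = √(2p(1 − p)/90.5), with the same assumed risk p in both arms.
- Chance that a true 10-point excess is non-significant, two-sided 5% = 1 − Φ(0.10/SE − 1.96).

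| Assumed risk | SE | 95% CI half-width | Chance not significant |
|---|---|---|---|
| 30% | 0.068 | 0.13 | 0.69 |
| 40% | 0.073 | 0.14 | 0.72 |
| 50% | 0.074 | 0.15 | 0.73 |

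The 10-point excess is an illustration, not a figure from the article. These values take clustering as properly handled.

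**The case against.** Several points on the other side stand.

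- A reader might infer that the planned analyses cannot yield a risk difference at all. The document does not support that. A test of proportions is listed first for objectives 1 to 3 and compares proportions directly. A logistic model can be standardised to a marginal risk difference, and an identity-link GEE on a binary improved/not improved outcome would give one. The methods as described are not directed at the hypothesis, but they could be.
- A reader might infer that the paired and unpaired tests ignore the community randomisation and so have an inflated type I error. The same section says that all analyses allow for clustering within communities, so an inflation figure would describe an analysis the protocol excludes.
- A reader might infer that non-significance will be reported as noninferiority. Nowhere does the article say so. It commits to CONSORT reporting for noninferiority trials and to both analysis sets.
- Objective 4 concerns extent as well as number. Mean-score models do address extent.
- Baseline factors are listed separately from observed differences and may include the stratification factors, so not every covariate is chosen after seeing the data.
- Before-after and baseline tests apply to objective 4 only. They are weak practice but do not themselves block a noninferiority conclusion.
- Interval method and covariate lists are often left to an analysis plan.

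The last point does not remove the finding. The article does not merely omit detail: it names particular tests for particular objectives, and those do not match its hypotheses in unit, scale or form.

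**Conclusion.** The point holds in a limited form. It is strong for objective 4, where no named analysis is aimed at the between-arm difference in the number of children improved and two of the named tests do not bear on the treatment comparison. It is weaker for objective 2, where suitable tools are planned but the Abstract applies the test of proportions to lesions and surfaces while the hypothesis counts children. For both, no analysis is tied to a confidence bound, and no numerical margin is given; without that number no analysis could complete the claim. The covariate rule is a separate, smaller weakness.

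In size, a difference test of the planned precision would leave risk differences of roughly 0.13 to 0.15 around the estimate unexcluded, and would miss a true 10-point excess in about 69% to 73% of trials. Those figures rest on 180 evaluable children per arm, the planning ICC holding for these outcomes, and assumed risks of 30% to 50%.

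**What to change.** 1. For objectives 2 and 4, make the child-level between-arm risk difference the estimate, with a 95% CI clustered on community (binomial GEE or standardised logistic model, with a small-sample correction for 30 communities). Judge it against the margin in both the intention-to-treat and per-protocol sets.
2. State the numerical margin for each of these objectives and define when a child counts as improved on COHRQoL and on dental anxiety, before outcome data are available.
3. For COHRQoL and anxiety scores, replace the paired and baseline tests with one clustered between-arm model of the follow-up score adjusted for the child's baseline score.
4. Replace adjustment for observed baseline differences with the two stratification factors and the baseline value of the outcome.

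No new data are needed: baseline and follow-up values are already collected and the strata are known at randomisation. The cost is a rewrite of the analysis paragraph plus two decisions that wording alone cannot supply, the margins and the definition of improvement. Recruitment is planned from March 2026, so both can be settled before outcomes exist.

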#### Economic Analysis

Costs and outcomes of the interventions will be quantified and analyzed. The costs of the intervention and subsequent dental treatment costs within the trial period will be assessed from the health provider’s perspective. The intervention cost will be recorded using a World Health Organization–developed program costing template called CostIt, using a bottom-up approach. Unit costs of the intervention, for example, salary and AgF, will be based on the budget record of the study. The costs of dental treatments required will be determined using the treatment item codes extracted from the participant’s dental records and unit costs based on the Child Dental Benefit Schedule. Cost-effectiveness and cost-utility analysis will be undertaken. The incremental cost-effectiveness ratio or the changes in net costs and health outcomes resulting from the intervention compared with the control will be calculated. The incremental cost-effectiveness ratio can be presented as follows:

ICER = (Ci – Cc) / (Ei – Ec)

where Ci and Ei are the net costs and effectiveness of the intervention and Cc and Ec are those of the control. In the cost-effectiveness analysis, the E component is a clinical outcome. For the cost-utility analysis, the outcome is the number of years weighted by the quality-of-life index derived from ECOHIS-4D [25]. A standard World Bank and World Health Organization Choosing Interventions that are Cost-Effective (WHO-CHOICE) discount rate of 3% will be applied to both costs and outcomes that occur after the first year [26]. Uncertainty analysis will be performed.

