## Introduction

### Background and Rationale

The interim report of the Select Committee into the Provision of and Access to Dental Services in Australia noted that the rate of potentially preventable hospitalizations was the highest among children aged between 5 and 9 years and was higher among Indigenous Australians and those living in remote locations [1]. The higher tooth decay experience of Australian Aboriginal children, in which the majority of the disease remains untreated [2], is believed, partly, to be due to unfavorable visiting patterns to dental care providers, associated with poor accessibility, cost, and the lack of cultural awareness by service providers [3,4]. Australian Aboriginal children experience dental decay at more than twice the rate of non-Aboriginal children. The current models of service delivery are failing to meet the needs, and most decayed teeth remain untreated. The management of dental decay in young children is challenging, and it is commonly undertaken under hospital-based dental general anesthesia.

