## Discussion

### Anticipated Findings

Access to timely dental care is a challenging issue confronting many people in rural and remote communities in Australia but is particularly acute for the Indigenous population. The remote communities tend to have smaller population sizes, and there are usually no dental services available within the community; the residents of the community will usually have to travel long distances to obtain care or wait for itinerant visits by public dental services or volunteer-based service providers. This then leads either to a delay in getting care or, worse, trying to access care only when in pain, which can sometimes lead to the required care only being able to be provided under general anesthesia. By using the skills of an Aboriginal health worker or practitioner, who would normally reside within a community, to deliver primary dental care, it is expected that the intervention will promote better access to timely dental care, thus mitigating the factors outlined earlier.

The use of AgF to stop caries progression has been tested worldwide and has been shown to be effective in arresting caries. The procedure is relatively simple and painless. The simple and painless application lends itself to use among populations where standard care options for the management of dental caries may not be feasible or practical and to test its potential application by an appropriately trained non-oral health practitioner. This study will test the application of AgF by an Aboriginal health worker or practitioner.

This trial will test the feasibility and effectiveness of applying AgF to carious primary molars of young Indigenous children in remote communities. The rate of arrestment will be compared with the rate of arrestment among children in control communities provided with the minimally invasive care using the ART and the HT. We will also test the feasibility of using digital images acquired via a smartphone to validate on-site clinical assessments undertaken by calibrated examiners. The findings have the potential to disrupt a model of care that relies principally on care delivered by an oral health professional team using local anesthesia and the dental drill. Validation of remote clinical assessment for dental conditions will enable the use of teledentistry technology to further improve access to dental care in remote communities by reducing the reliance on care delivered by visiting dental teams.

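### The stated costing rule for follow-up treatment names no hospital, theatre or anaesthetic cost, so the objective 5 cost comparison is biased if hospital dental admissions differ between arms

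*Protocol article*

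**What the plan says.** Objective 5 (protocol article, Objectives) sets the hypothesis that "the intervention will be less costly with a noninferior outcome".

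The Economic Analysis section defines what is counted. Besides the intervention itself, "subsequent dental treatment costs within the trial period will be assessed from the health" provider's perspective. Intervention costs come from a costing template and the study budget. For later treatment, the section fixes both the quantity and the price. "The costs of dental treatments required will be determined using the treatment item codes extracted from the participant" (the sentence continues with that participant's) "dental records and unit costs based on the Child Dental Benefit Schedule". The cost difference Ci – Cc is then the numerator of the incremental cost-effectiveness ratio. An uncertainty analysis is promised without detail.

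Elsewhere the article makes hospital care part of its case. Background and Rationale says of decay management in young children that "it is commonly undertaken under hospital-based dental general anesthesia", and reports that "the rate of potentially preventable hospitalizations was the highest among children aged between 5 and 9 years". Anticipated Findings describes late, pain-driven attendance, "which can sometimes lead to the required care only being able to be provided under general anesthesia", and expects the intervention to mitigate these factors.

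The section on concomitant care lets children use their usual dental provider and says that participants will be asked at each follow-up about treatment since the last visit. The Economic Analysis section does not name those answers as a costing source. The Outcomes section does not list admissions or treatment under general anaesthesia.

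**The concern.** The quantity source is a dental record and the price list is a dental benefit schedule. Neither is described as holding the cost of a hospital bed, an operating theatre or an anaesthetist. The same extraction in a community clinic and in hospital under general anaesthesia would then enter the analysis at much the same value, although the second uses further resources.

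The trial population makes this relevant. Children are eligible from 6 months to 7 years and are followed for 2 years, so those enrolled at 3 years or older are aged 5 to 9 for some or all of follow-up. That is the age band that the Background singles out for preventable hospitalization.

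At stake is the less-costly half of the objective 5 hypothesis. If the arms differ in admissions, the numerator of the ratio omits part of the real difference, and the ratio carries that error into the evidence on models of care that the trial is meant to supply. The primary clinical outcome and the sample size are not affected.

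**Working it through.** The plan states no cost figure, so there is none to reproduce. The check follows one child through the rule and then asks how large the omission could be.

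**1. One child under the rule.** Let f be the dental item fees for a course of treatment and H the hospital, theatre and anaesthetic cost of one admission.
- Treated in a clinic: cost incurred f, cost counted f.
- Treated in hospital under general anaesthesia: cost incurred f + H, cost counted f at most.
- Omitted per admission: H.

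This assumes that the schedule has no price for the H component, which the article neither states nor denies.

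**2. Effect on the comparison.** Let d be admissions per child in the intervention arm minus those in the control arm. Then

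counted (Ci – Cc) = full (Ci – Cc) – d × H.

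If d = 0 there is no bias. If d > 0 the intervention looks cheaper than it is. If d < 0 part of its saving is lost.

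**3. Illustrative size.** The 320 children per arm come from the Sample Size section. The values of H and d are assumptions.

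| Difference d | Admissions among 320 | H = A$2,000 | H = A$4,000 | H = A$8,000 |
|---|---|---|---|---|
| 2 points | 0.02 × 320 = 6.4 | A$40 | A$80 | A$160 |
| 5 points | 0.05 × 320 = 16 | A$100 | A$200 | A$400 |

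The last three columns are d × H, the amount per enrolled child missing from the comparison.

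**4. When the ranking would reverse.** Let S be the counted saving per child in the arm that looks cheaper. The ranking reverses when that arm's excess admissions per child exceed S / H. With assumed S of A$50 to A$500 and H of A$2,000 to A$10,000:
- lowest threshold: 50 / 10,000 = 0.5%, or 0.005 × 320 = 1.6 admissions;
- mid-range: 200 / 5,000 = 4%, or 0.04 × 320 = 12.8, about 13 admissions;
- highest threshold: 500 / 2,000 = 25%, or 0.25 × 320 = 80 admissions.

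The range is too wide to say that a reversal is likely. It does show that a modest imbalance would be enough where the counted saving is small relative to the cost of an admission.

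**5. Could the planned analysis pick this up?** An uncertainty analysis can vary only what has been measured or assumed. No admission count and no hospital price is planned as an input.

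**The case against.** The strongest reply has four parts.

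- **The article does not say that hospital costs are excluded.** It says how dental treatments are priced, and a condensed article may leave a fuller cost list to a document not shown. It is true that there is no express exclusion, and a reader should not infer one. But the article does not leave a blank: it names a record source and a price list, and on a plain reading both are dental. If a fuller document adds hospital costs, one sentence here would settle the matter.
- **The schedule's contents are inferred.** This stands, and the conclusion is conditional on it.
- **The perspective is a declared choice.** The article does not say whether the health provider bears hospital costs, so a narrow costing might be deliberate. This stands as a reason to report both versions. It does not explain why the care used to motivate the trial is left unmentioned in the costing.
- **Admissions may not differ.** Both arms receive active care, children needing urgent care are excluded and referred, and comprehensive care including extractions is offered. The Background also cites a trial in which minimally invasive care managed children recommended for general anaesthesia. These points could make any difference small. That trial used the control arm's techniques, however, so it says little about the silver fluoride arm.

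Two stronger readings are tempting and are not supported. One is that the article presents general anaesthesia as the main or costliest consequence of decay. It says commonly in one place and sometimes in another, gives no cost, and the Abstract mentions hospitalizations only. The other is that silver fluoride will be declared cheaper while sending more children to hospital. No admission rate is given for either arm, and the bias could equally hide a saving.

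**Conclusion.** The point holds as a conditional one. Followed as written, the costing counts at most the dental fees of treatment under general anaesthesia, and the planned comparison of costs is biased by d × H whenever admissions differ between arms. Under the assumed A$2,000 to A$8,000 per admission, the missing amount is A$40 to A$160 per child for a 2-point difference and A$100 to A$400 for a 5-point difference.

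The conclusion rests on three assumptions: that the schedule has no hospital or anaesthetic price, that no document outside the article adds one, and that admissions differ between arms. Neither the direction nor the true size can be derived from the article. The matter concerns a secondary but named hypothesis. It is worth settling before follow-up starts, because admissions not recorded at the time may be hard to recover later.

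**What to change.** In the Economic Analysis section, state that:

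1. Hospital admissions for dental treatment from baseline to 24 months are counted per child, using the existing follow-up question on interval treatment with an explicit item on hospital or general anaesthesia care.
2. Each admission is costed at a hospital unit cost that includes theatre and anaesthetic, with its source named.
3. Ci – Cc and the ratio are reported with and without this component, stating which version matches the declared health provider's perspective.
4. The number of admissions is reported by arm beside the cost result.

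The cost is one added item at two existing visits, one unit cost, and a few lines of text. Recruitment is planned to begin on 1 March 2026, so under that timetable the first 12-month visits come no earlier than March 2027.

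There are real downsides. The count depends on parents' recall over up to 12 months. It will also be missing for children lost to follow-up: the plan allows 25% loss a year, which leaves 320 × 0.75 × 0.75 = 180 per arm at 24 months. Infrequent, expensive events will also make the cost difference more variable.
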